## Abstract

**Background:**

Perinatal mental health difficulties can negatively impact maternal wellbeing, which in turn can impact the mother-infant bond. Although parenting interventions have been found to be effective, they are often not routinely offered in mental health services as additional psychosocial support. Thus, the aims of this study are a) to examine the feasibility of recruiting mothers, engaging them in an online parenting intervention and retaining them in the study and b) to explore the acceptability of this type of intervention in mothers and specialist perinatal mental health staff. We will also explore any changes in relevant outcomes for mothers.

**Methods:**

In this uncontrolled feasibility study, women experiencing moderate to severe mental health problems, who are in the later of stage of their pregnancy or mother to a baby up to 12 months old, will be recruited from a perinatal community mental health service in the Northwest of England, UK. Consented participants will be offered the self-paced Triple P for Baby Online parenting intervention alongside any service support. To support engagement, the research team will offer four check-in phone calls and text messages to support participants. Outcomes measures, completed online at baseline and again at post-intervention ten weeks after study enrolment, will examine changes in maternal mental health (depression, anxiety, stress), wellbeing, maternal self-efficacy and the perceived mother-infant bond.

**Results:**

Descriptive summaries will be produced for feasibility outcomes, including recruitment and retention rates and number of sessions completed. We will use paired t-test or Wilcoxon signed rank test for pre- and post-intervention questionnaire data and the reliable change index to explore any changes in outcomes. Mothers (n=10-20) and staff (n=5-10) will be interviewed to explore acceptability, engagement and implementation factors. Interview data will be analysed using framework analysis.

**Discussion:**

This is the first study to examine the feasibility of engaging women in a self-paced, online parenting intervention and its acceptability within a NHS perinatal community mental health service. We will also explore its potential benefits in terms of outcomes. If progression to a full trial is indicated, this study will inform future study design, recruitment methods, eligibility criteria and outcome measures.

**Trial registration:**

Prospective ISRCTN registration (11/03/2025): ISRCTN87365121; https://doi.org/10.1186/ISRCTN87365121.

## Introduction

1

Parenting interventions have consistently demonstrated strong effectiveness and efficacy in promoting positive developmental outcomes for both parents and children, with benefits ranging from improved parenting skills and reduced child behavioural problems to overall enhanced family functioning (1, 2). Among these interventions, the Triple P–Positive Parenting Program stands out as one of the most extensively researched, evidence-based, and scalable frameworks (3–7). Grounded in social learning theory, cognitive-behavioural, and developmental psychology, Triple P has been shown to reduce coercive parenting, increase parental self-efficacy, and significantly decrease child conduct problems across diverse populations and cultural contexts (3, 4, 7–11). Meta-analytic evidence further indicates that parenting programmes like Triple P foster long-term gains in child emotional regulation, decrease parental stress, and strengthen parent–child relationships, highlighting their value as both preventative and therapeutic tools (3, 4, 7, 8, 12, 13). Collectively, structured, evidence-based parenting interventions play a critical role in supporting family resilience, promoting healthy child development, and reducing the burden of mental health and behavioural difficulties across communities. Although the majority of evidence focuses on parenting programmes for preschool and school-aged children, similar principles of early relational and psychoeducational support underpin interventions designed for infants.

The transition to parenthood represents a major developmental milestone characterised by profound psychological, relational, and practical adjustments (14, 15). New parents frequently experience elevated stress, sleep disruption, and changes in couple functioning, all of which heighten vulnerability to perinatal mental health difficulties, such as depression and anxiety (16, 17). Parental mental health is closely intertwined with the quality of early caregiving behaviours (18, 19). Parental distress can undermine sensitive and responsive caregiving, whereas supporting parents to feel competent, regulated, and emotionally available strengthens the emerging parent–infant bond (20–22). This bond forms the foundation for infants’ emotional regulation, attachment security, and later socio-emotional development (15, 23–25). As interventions that support and strengthen parental wellbeing alongside early relationship-building are vital for fostering healthy developmental trajectories in both parent and child (26), there has been an increased focus by governments, especially in the United Kingdom (UK), to make the provision of early intervention, enhanced perinatal mental health services and support for vulnerable families a national priority (e.g., 27–29).

Triple P for Baby was developed to support new parents (e.g., mothers, fathers, etc.) transitioning to parenthood by targeting known modifiable risk and protective factors (30–32). It promotes realistic expectations about parenthood, the couple’s changing relationship, infant behaviour and development, whilst offering parenting skills training to increase parenting competence and adaptive strategies for emotion regulation. Through Triple P’s underlying self-sufficiency model (3–5, 13) Triple P for Baby also seeks to equip parents with knowledge and skills as well as the confidence to independently manage common parenting challenges. It promotes the development of a strong parent-infant bond, the strengthening of the parents’ coping resources and the improvement of both parents supporting each other whilst drawing on wider social support (30–32).

Triple P for Baby was originally designed as a four-session antenatal group intervention, followed by four postnatal individual telephone support sessions, but it has been delivered individually and postnatally only as well. Triple P for Baby’s acceptability and feasibility and potential benefits have been demonstrated in various studies including randomised controlled trials with primiparous and multiparous parents in diverse settings (e.g., 31–44). For example, a larger UK RCT involving first-time parent couples demonstrated strong compliance and engagement with the programme, indicating its practical acceptability (38). However, a follow-up sensitivity analysis of a sub-sample of data revealed limited effects on the couple relationship, social support and parenting skills. But caution should be exercised in the interpretation of these findings because the sub-sample was underpowered (38). Furthermore, a large UK RCT comparing an enhanced version of Triple P for Baby and Mellow Bumps against standard care in a group of women with complex social and care needs did not demonstrate efficacy for any parenting intervention in improving mental health and wellbeing outcomes for women in this context of heightened social complexity (37).

Despite being a universal parenting intervention, Triple P for Baby has also been explored as an additional treatment for women with mental health problems; for example, in a pilot RCT with mothers experiencing postnatal depression reported high levels of participant engagement and satisfaction (42). Furthermore, a multi-site feasibility RCT evaluated the individually and postnatally delivered intervention in a perinatal mental health setting (psychiatric Mother and Baby Unit) and reported that 75% of mothers completed the intervention, which these mothers also rated as highly acceptable (44). Clinical outcomes signalled potential improvements in parenting competence, bonding, mood and mental health symptomatology, but a full trial in a specialist perinatal mental health setting in the UK has yet to be undertaken. Finally, a full RCT in an urban Kenyan setting, with Afrikan mothers experiencing depression and anxiety, showed improvements in maternal mental health outcomes, but no significant difference was found in maternal self-efficacy between the mothers who did and those who did not access Triple P for Baby (33).

The COVID-pandemic in 2020 accelerated the development of online interventions including a seven-session, self-paced, self-guided, interactive version of Triple P for Baby Online. It is highly accessible (via laptop, tablet or phone) to parents of infants, minimising the need for external childcare to attend the intervention in person and, given its interactive content with brief video-clips, it is also suitable for people with different literacy and educational levels. Online versions of Triple P have been shown to be as effective as other modalities in general population samples (3, 4, 45). In 2022, a national rollout of Triple P Online took place across Australia which allowed all families with children under 12 years of age across the country free access to Triple P’s evidence-based suite of online programmes, including the intervention for parents of babies (46). Similarly, the strength of Triple P for Baby’s existing evidence and its ability to support parental wellbeing and the parent-infant-relationship led the Department of Health and Social Care and NHS England in 2021 to commission the training of 680 practitioners in this intervention as part of the *Start for Life/Family Hub* offer for 75 local authorities (47). Many local authorities also commissioned the delivery of Triple P for Baby Online to address the Department of Work and Pensions’ Reducing Parental Conflict Programme (48) and the *Supporting Families Outcome Framework* (49).

With an increasing emphasis on digital approaches to improving mental health care, the proposed project allows us to explore the feasibility and acceptability of this parenting intervention whose online version has not yet been tested in a perinatal mental health context. Triple P for Baby Online is an ideal supplementary intervention to strengthen parenting competence, the parent-infant bond and partner support – important factors which are not always targeted by perinatal mental health services.

Up to 27% of women experience maternal mental illness in the perinatal period (50), with maternal suicide being the leading cause of death for women between six weeks and one year after pregnancy in the UK (51). In the UK, perinatal mental health services have been expanded to improve access to assessment and treatment for women as a public health priority (29, 52, 53). This increased access is expected to minimise the risks that maternal mental illness can pose for the development of bonding and attachment difficulties between mother and baby and any subsequent negative impacts on the child’s development (18, 54, 55).

The type and severity of the woman’s mental health problem in the perinatal period will determine the type of intervention offered (56). In England, 81,975 women were referred to a specialist perinatal mental health service from 04/2023-03/2024, with 66.65% (n=54,635) having a first face-to-face appointment (57). If accepted by a perinatal mental health service women are offered psychological interventions (predominantly focused on the mother) (58–60), usually delivered individually or in a remote group format by two facilitators, depending on mental health severity and safeguarding concerns. Couples therapy to reduce relationship conflict during the perinatal period is not offered consistently, if at all. Parent-infant psychotherapy referrals are made only for bonding difficulties. Given the substantial long-term negative effects of early adverse experiences (18, 55) and the capacity of positive relationships to buffer these effects (61, 62), strengthening the mother-infant-relationship is important (63). However, parenting interventions are not routinely offered in perinatal services, despite their established evidence-base in improving child and parent outcomes and reducing child maltreatment.

By examining the feasibility and acceptability of Triple P for Baby Online as a supplementary intervention, this study is the first step towards insights related to improvements in intervention access and mother and infant support in specialist perinatal services. Thus, the aims of this uncontrolled study are 1) to examine the feasibility of recruiting and engaging mothers with perinatal mental health difficulties in an online parenting intervention and retaining them in the study and 2) to explore the acceptability of this type of intervention in mothers and perinatal mental health staff. We are also interested in exploring any implementation factors associated with engagement and retention and if there is any change over time in outcome measures of maternal mental health, wellbeing, maternal self-efficacy and the perceived mother-infant bond.

## Methods

2

### Design

2.1

The study is an uncontrolled feasibility study, with a qualitative component exploring the intervention’s acceptability with participating mothers and staff. Indicators for psychological change over a ten-week follow-up period will be explored by pre- and post-intervention outcome measures. This uncontrolled, pre- and post-intervention design was chosen to focus on acceptability and feasibility of the intervention and to collect data to determine if the study procedures, outcome questionnaires and Treatment As Usual (TAU) as a comparative arm for a future trial are feasible.

**Figure 1** provides an overview of the study design based on CONSORT guidelines (64). For transparency, this protocol is reported in line with the SPIRIT checklist for protocols of randomised trials (65), although any items related to randomisation and blinding (21a-24c) have been omitted from this protocol because we are describing a non-randomised trial. The TIDieR checklist for the reporting of interventions (66) has also been used (see **Supplementary Materials**).

**Figure 1 f1:**
[figure not shown]
CONSORT diagram showing study design.

### Ethical approvals and research governance

2.2

The study has been approved by the National Health Service (NHS), Health Research Authority and the Greater Manchester Mental Health NHS Foundation Trust (IRAS ID: 352080). It will be conducted in accordance with the local legislation and institutional requirements. Amendments to ethical approval will be sought in the event of protocol modification. Participants will provide informed consent to participate in the study. The University of Manchester will provide oversight as the study sponsor. All staff will be trained in research governance principles (e.g., Good Clinical Practice, data protection and information governance). A Patient and Public Involvement and Engagement (PPIE) group comprising mothers with lived experience of perinatal mental health difficulties will be consulted on various aspects of the study such as content of the support calls and text messages and the topic guide. The PPIE group will convene at four scheduled meetings during the study and provide support via email between meetings. The intervention is low risk so there will not be a standard provision of ancillary and post-trial care.

### Study setting

2.3

In this single site study, participants will be recruited from a specialist perinatal mental health community-based service, covering three large geographical areas in Greater Manchester, England, for women experiencing moderate to severe mental health problems in the perinatal period. Women referred to the service are assessed and, if eligible, assigned to a particular treatment pathway (e.g., the psychology pathway or the occupational therapy pathway). For this study, we will recruit from the psychology pathway. Mothers assigned to this pathway are typically offered individual or group specialist psychological interventions to meet their complex needs.

### Inclusion and exclusion criteria for participants

2.4

Participants are eligible if they are a) in the third trimester of pregnancy or the mother or birthing parent of an infant aged birth to 12 months, with whom they live, or have parental responsibility for, b) aged 18 years or older, c) proficient in English to engage with the intervention and complete assessments (and take part in interviews), d) capable of giving informed consent. Participants also need to have been accepted onto the psychology pathway of the service and own or have access to a smartphone, tablet, laptop or computer to access the intervention. As Triple P for Baby Online is a supplementary intervention that participants can engage with alongside any psychological treatment, participants will not be excluded if they engage in other interventions typically offered by this service. Participants will be excluded if they are or become inpatients at the time of recruitment, because inpatient admission usually signals that additional risk factors are present (e.g., suicidal ideation or behaviours) that cannot easily be managed in a community setting.

### Sample size considerations and recruitment

2.5

We plan to recruit a minimum of 30 participants, which is a typical and recommended sample size for feasibility studies (67, 68). As codes for the intervention are only available for 100 participants as a minimum, we could recruit up to 100 participants.

Potential mothers will be identified by perinatal mental health staff, such as the team’s clinical psychologist or assistant psychologist. Staff will consider who on their waiting lists or caseloads might be eligible and then provide them with brief information about the study in the form of an advert, or a brief study summary. Members of the research team will also attend weekly referral and allocation meetings to support staff with recruitment and potential participant identification and reduce potential selection bias. If staff have concerns about a woman’s capacity or mental state (e.g., suicidal ideation or behaviours), they would not consider that participant to be eligible.

Mothers (and birthing parents) interested in taking part will be asked for verbal consent to be contacted by a member of the study team who will then contact them to provide further information and conduct an eligibility screening. Alternatively, potential participants can self-refer to the study via a link in the study advert which staff can email to interested mothers. Potential participants will be provided with a participant information sheet and given at least 48 hours to read it. A follow-up phone call will be arranged for a mutually convenient time to answer any questions and discuss their interest in taking part. Reasons for non-participation will be collected and anonymised with potential participants’ verbal consent to inform feasibility and acceptability.

Eligible individuals who decide to participate will be enrolled to the study. A researcher will obtain their audio-recorded informed consent to take part in the study including personal identifiable information (e.g., full name, date of birth) and complete a pseudonymised electronic copy of the consent form. Identifiable information will be stored securely and separately from the study data and deleted once it is no longer needed for study purposes. The audio-recorded consent and the pseudonymised consent form will also be stored separately from one another to maximise data protection. Baseline assessment may also be conducted or started at this appointment (depending on participant preference).

Using convenience sampling, ten to 20 mothers who have participated in the study for at least seven weeks will be invited to take part in interviews to explore study and intervention acceptability qualitatively. If a large number of participants indicate interest in attending an interview, we will prioritise contacting participants with different demographic characteristics and engagement with the intervention and/or the study procedures to capture diverse views and experiences. For staff interviews, we will purposively sample five to ten staff to include a range of job roles and perinatally relevant work experience. Staff are eligible to take part if they are a healthcare professional working for this service (e.g., a clinical or counselling psychologist, CBT therapist, nursery nurse, team leader, assistant psychologist). They will be excluded if they have been in post for less than six months to ensure staff participants are familiar with the service and its service users. Separate consent to take part in an interview will be sought from mothers and staff.

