### Feasibility outcomes

2.7

Feasibility will be assessed by examining data related to recruitment and study retention (i.e. completion of outcome measures at follow up). To evaluate the suitability of this study to progress to a larger, randomised trial, we will use the red, amber, green (RAG) system and pre-determined progression criteria (70–72). **Table 2** provides an overview of our proposed progression criteria. We will also report on a range of feasibility indicators (e.g., number of potential participants found to be eligible, reasons for declining to participate, the extent and pattern of missing data, the number of related adverse events, etc.). In addition, the Triple P Online Management system will allow the research team to monitor participants’ progress through the programme and aggregate relevant feasibility data on engagement (e.g., how many and what sessions were completed, dates of first and last log-ins, number of log-ins per participant).

**Table 2 T2:** Progression criteria for feasibility.

Indicator	Green	Amber	Red
Recruitment: number of eligible participants recruited within our recruitment window of 29 weeks	≥ 60% = green	50–59% = amber	≤ 49% = red
Study retention: proportion of participants completing measures at each data collection point (baseline and follow up)	≥70%	50-69%	≤49%

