### Acceptability outcomes

2.8

Intervention acceptability will be assessed quantitatively via the Client Satisfaction Questionnaire (73), administered to participants at follow up via the online survey tool, Qualtrics. Participants will be asked to answer 13 questions (rated on a 7-point Likert scale) and three open-ended questions (e.g., Do you have any other comments about the programme)?.

Qualitative exploration of acceptability will be conducted via online interviews with a sub-group of participants and staff. Acceptability in this context will focus on the exploration of attitude towards the intervention, intervention and assessment burden, and facilitators and barriers towards uptake and engagement with the intervention, as informed by Sekhon et al.’s (74) theoretical framework of acceptability.

Separate consent for this aspect of the study will be sought. Interviews will explore participants’ views of the intervention content, mode of delivery, the encouraging phone calls and text messages, and the study procedures, such as assessment burden. We will also conduct exit interviews with mothers who withdraw from the study, if possible.

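### Mothers are interviewed by convenience sampling and varied engagement is sought only if many volunteer, so enrolled mothers who use little of the programme may be under-represented

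*Protocol article*

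**What the plan says.** Section 2.5 of the protocol article governs who is interviewed. For mothers: "Using convenience sampling, ten to 20 mothers who have participated in the study for at least seven weeks will be invited to take part". Engagement enters only conditionally: "If a large number of participants indicate interest in attending an interview, we will prioritise contacting participants with different demographic characteristics and engagement". The article does not say how many volunteers count as a large number, and it sets no minimum for any engagement level. For staff, the same paragraph is unconditional: "we will purposively sample five to ten staff to include a range of job roles and perinatally relevant work experience".

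The interviews serve a stated purpose. Section 2.8 lists among their topics "facilitators and barriers towards uptake and engagement with the intervention", and the Introduction adds an interest in "exploring any implementation factors associated with engagement and retention". The Discussion says the study will identify how the intervention needs tailoring for this group.

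Three other provisions bear on the point:

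- Section 2.8: "We will also conduct exit interviews with mothers who withdraw from the study, if possible".
- Section 2.5: "Reasons for non-participation will be collected and anonymised with potential participants’ verbal consent to inform feasibility and acceptability".
- Section 2.7: the Triple P Online Management system records "how many and what sessions were completed, dates of first and last log-ins, number of log-ins per participant".

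**The concern.** Mothers who enrol and then use little of the programme are the most direct source on barriers to engagement. Under the default rule nothing steers invitations towards them. The provision that would do so operates only when volunteers are plentiful. It is off when volunteers are few, which is when self-selection matters most.

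The programme is self-paced with 12 months of access (section 2.6), so a mother can stop logging in without withdrawing from the study. If few such mothers are interviewed, the account of barriers will be thin, and tailoring for a full trial will lean on those for whom the programme worked well enough to continue. Table 2 has progression criteria for recruitment and retention but none for programme use, so the interviews are a main source for understanding poor engagement.

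**Working it through.** The range of 10 to 20 interviews is planned, not calculated, so there is no figure in the plan to reproduce. The check has two parts.

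**1. Which route reaches an enrolled mother who uses little of the programme and does not withdraw?**

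| Route | Whom it reaches | Does it secure her? |
|---|---|---|
| Convenience interviews (2.5) | Mothers at least seven weeks in the study | Eligible, but not sought |
| Diversity clause (2.5) | Varied engagement, if many volunteer | Only if triggered; no threshold |
| Exit interviews (2.8) | Study withdrawers, where possible | No |
| Reasons for non-participation (2.5) | Women who decline to enrol | No |
| Satisfaction questionnaire at follow-up (2.8, 2.9) | All participants asked | Only if she responds |
| Platform data (2.7) | All registered users | Shows that she stopped, not why |

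**2. How large could the shortfall be?**

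Inputs from the article: at least 30 participants and possibly up to 100 (section 2.5); 10 to 20 interviews (section 2.5); 75% completion in an earlier Mother and Baby Unit trial of the individually delivered version (Introduction). No completion rate is given for the online version in this setting.

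Assumptions: N = 30. Non-completers are 25% of 30 = 7.5, taken as 8. A non-completer's odds of volunteering are ω times a completer's, with ω = 1, 0.5 or 0.25. The article gives no value for ω.

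Model (Fisher's noncentral hypergeometric), with X the number of non-completers among n interviewees:

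P(X = x) ∝ C(8, x) · C(22, n − x) · ω^x

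| Interviews n | ω | Expected non-completers | P(at most one) |
|---|---|---|---|
| 10 | 1 | 2.67 | 15% |
| 10 | 0.5 | 1.80 | 41% |
| 10 | 0.25 | 1.12 | 69% |
| 15 | 0.5 | 2.97 | 10% |
| 15 | 0.25 | 2.04 | 33% |
| 20 | 0.5 | 4.36 | 0.6% |
| 20 | 0.25 | 3.38 | 4.6% |

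If 15 of the 30 are non-completers, 10 interviews give P(at most one) of 3% at ω = 0.5 and 15% at ω = 0.25.

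A second view treats the engaged share as unknown. Let e be the share of participants who engage, and r how many times likelier an engaged mother is to be interviewed. The engaged share of interviewees is e·r / (e·r + 1 − e):

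| e | r = 1 | r = 2 | r = 3 |
|---|---|---|---|
| 0.30 | 30% | 46% | 56% |
| 0.50 | 50% | 67% | 75% |
| 0.75 | 75% | 86% | 90% |

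For example, e = 0.50 and r = 2 gives 1.0 / (1.0 + 0.5) = 67%.

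Limit of the illustration: non-completers are not the same as low engagers. A mother with six of seven sessions is a non-completer but clearly engaged. The article gives nothing from which to estimate how many will complete few or no sessions.

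**The case against.** Convenience sampling is openly declared, is common in a small qualitative component and contradicts nothing else in the article. The seven-week condition is time in the study, not programme use, so a mother who never logs in remains eligible. The plan already names engagement as a criterion when it can choose among volunteers. Thirty is a floor, and with recruitment nearer 100 the diversity clause would apply more readily. Acceptability evidence also comes from the satisfaction questionnaire with its open questions, from staff interviews and from the platform data. If about 75% complete, a sample made up mostly of completers simply mirrors the cohort.

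Most of this stands, and it limits the point. In particular, a reader might infer that the acceptability and barriers objective will mostly be answered by women who engaged, or that acceptability will look better than it is. The article does not support either as a prediction. It gives neither the engagement rate nor the pattern of volunteering, and at 30% engagement the engaged share of interviewees could be anywhere from 30% to 56%. Nor does it support reading the seven-week rule as selection on engagement.

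What the objection does not remove is the gap itself. Each of the other routes is aimed at a different group, depends on response, or records disengagement without its reasons. Mirroring the cohort is also not enough when the question is about barriers: with 10 interviews and 8 non-completers among 30, even equal volunteering leaves a 15% chance of hearing from at most one.

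**Conclusion.** The point holds as a risk. Selection by engagement is conditional, its trigger is undefined and no minimum is set, so enrolled mothers with little programme use may be under-represented on a topic the interviews are meant to cover. The other sources offset this only in part.

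The size cannot be fixed from the article. Under the illustrated assumptions (30 participants, 8 non-completers, odds of volunteering one half to one quarter), the chance of at most one non-completer among the interviewees is 41% to 69% with 10 interviews, 10% to 33% with 15, and 0.6% to 4.6% with 20. It is lower if non-completion is more common. The risk therefore matters near the bottom of the planned range and is small near the top. No stated number in the plan is affected. This is a cheap improvement to the qualitative sampling, not an error that undermines the study.

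**What to change.** Replace the default convenience rule for mothers with purposive invitation across engagement levels from the outset, using the session counts from the Triple P Online Management system. Include mothers with few or no sessions who have not withdrawn. Let the team set a target for low engagers that is feasible given how many there turn out to be. A rigid quota such as 4 of the first 10 interviews is not advisable: with only 8 non-completers among 30, and presumably fewer mothers at very low session counts, it would need half or more of that group to agree. Keep the total at 10 to 20, aim above the lower end where possible, and report interviewees' session counts beside those of all participants.

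The cost is a change of wording, possibly a minor amendment, and more invitations per completed interview, since low engagers may respond less often. The total number of interviews does not rise. The article describes recruitment as ongoing; if interviews have begun, the remaining invitations can still be directed this way, and the comparison of session counts can be reported in any case.
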